### Interventions

The PRB uses two approaches to implementation: the NIATx organizational change model within a multi-organizational learning collaborative in the intervention arm and online PRB resources in both study arms. The PRB includes:Candidate identification strategies for finding prescribers interested in prescribing OUD pharmacotherapies. The Ohio “To Test a Payer/Treatment Agency Intervention to Increase Use of Buprenorphine” found the following physician specialties to be more likely to become opioid pharmacotherapy prescribers: (a) addiction medicine specialists, (b) psychiatrists who are already practicing within the organization, and (c) family medicine and internists in the community. Similarly, Rosenblatt et al. [24] observed that 81.9% of physicians with a Drug Enforcement Administration (DEA) waiver to prescribe buprenorphine came from a combination of the psychiatry, primary care, and addiction medicine specialties. The bundle recommends seeking physician prescribers from these specialties and to be aware that as of 2016, advanced practice nurses and physician assistants can also now prescribe buprenorphine [25].Prescriber education forum slide deck that can be used to inform prescriber groups and stimulate interest in OUD pharmacotherapy prescribing. Potential prescribers are often unaware of the practice opportunities in addiction medicine. Once they are aware of those opportunities, they are more likely to provide care to patients with addiction disorders [26]. Education forums can describe practice opportunities in the addiction field, how physicians and other clinicians can reduce the impact of OUDs, and give medical professionals the opportunity to express their interest in becoming OUD pharmacotherapy prescribers. The slide deck is intended for use by agency staffPrescriber-friendly workflow and risk-reduction strategies that provide clinical supports to assist prescribers with managing OUD pharmacotherapy patients. Two concerns of potential prescribers are that patients on opioid treatment pharmacotherapies require added effort and that these patients present additional clinical risk [27]. LaBelle et al. [28] reported that the use of nurses to assist physicians with the provision of buprenorphine treatment has led to expanded use of this pharmacotherapy. This strategy reduces the clinical workload on prescribers and allows for the use of a risk management plan based on existing clinical guidelines that also prevents the non-medical use or diversion of buprenorphine prescriptions [29]. Education can also be provided on how buprenorphine side effects and mortality are low, and side effects are less severe than other comparable opioid treatment alternatives [3].Academic detailing to recruit OUD prescribers. Academic detailing is an evidence-based tool to influence prescriber decision making and to recruit OUD prescribers. Developed by Soumerai et al. [30], academic detailing uses persuasive communication to influence physician behavior [31, 32]. This approach applied to recruiting OUD pharmacotherapy prescribers includes the following steps: (1) conducting interviews to investigate baseline knowledge of and motivations for buprenorphine treatment, (2) defining clear educational behavioral objectives, (3) establishing credibility by citing authoritative and unbiased sources of information and presenting both sides of controversial issues, (4) stimulating active physician and clinician participation in educational interactions, (5) using concise graphic educational materials, (6) highlighting and repeating the essential messages, and (7) providing positive reinforcement during follow-up visits. Agency staff are encouraged to use academic detailing strategies as part of physician recruitment.Telemedicine to provide access to OUD pharmacotherapies. Barriers of time and distance can limit access to OUD prescribers [11]. Buprenorphine prescribing physicians are often clustered in urban centers [24]. Some behavioral health organizations have begun to use telemedicine to increase patient access to services that are not available or if more capacity is needed in a given clinic [33–35]. For buprenorphine care, a buprenorphine prescriber can use videoconferencing to treat a patient at a remote location. Resources will be available in the PRB explaining how to use telemedicine for buprenorphine care to increase access to care and patient convenience.Promoting organizational leadership and culture to support the building of OUD pharmacotherapy capacity. Leadership and culture that supports use of opioid treatment pharmacotherapies, and the recruitment of OUD pharmacotherapy prescribers facilitates provision of this evidence-based practice [36]. Specific actions leaders can take to support recruitment include providing resources for recruiting and creating an attractive environment for applicants [37]. Examples of how to apply leadership skills to promote medication-assisted treatment use will be also included in the PRB.

In the intervention arm, the PRB implementation will begin with a 4-month planning phase to identify practices that are not present or underutilized in the study sites. They will then be implemented in the rollout phase (Fig. 2). Within each treatment organization, we will engage management to participate in PRB practices: a top leader (the executive sponsor), the primary physician recruiter for the organization (the change leader) if different from the executive sponsor, and the clinical director.

**Fig. 2 Fig2:**
[figure not shown]
PRB implementation sequence (during the 24-month intervention period). *OUD* opioid use disorders, *PRB* Prescriber Recruitment Bundle, *MAT* Medication-Assisted Therapy

During the planning phase, key components of the PRB implementation process (designed based on the evidence-based NIATx organizational change model [38, 39] include (1) defining the aim through a briefing between the executive sponsor and a project coach provided by the research team, (2) assessing PRB baseline to measure level of use of the different PRB practices and document the existing buprenorphine slots availability and extended-release naltrexone capacity, and (3) training leadership and prescriber recruiters to develop and implement an organizational change or a new practice from the bundle. The training will include all organizations within the state that were randomized to the intervention arm to encourage cross-organizational sharing. After the planning phase, a 20-month rollout phase occurs that includes (4) monitoring progress in increasing the number of buprenorphine slots, extended-release naltrexone capacity, and use of the PRB; (5) pilot testing of changes to implement and enhance PRB implementation using the evidence-based Plan-Do-Check (or measure)-Act approach [40]; and (6) sustaining successful changes by implementing a plan to institutionalize gains and avoid reverting to the old system.

Throughout the planning and rollout phases, each organization will have a coach. The coach is an expert in prescriber recruitment, OUD treatment, and organizational change who supports treatment organizations as they make, sustain, and spread PRB practices. Coaches help organizations think through key issues, offer process improvement training, and suggest changes during monthly coaching calls and e-mails as needed.

### Timeline

During project months 1 to 18, the study team will design the PRB intervention, complete IRB approval, and identify and recruit treatment organizations. In months 14 to 18, the study team will collect baseline data on number of assigned and open buprenorphine slots and extended-release naltrexone capacity. In months 15 to 42, the study team will implement the study arm interventions and collect outcome data on the 24-month staggered start intervention. During months 37 to 52, the study team will collect quantitative data on the sustainability of the changes. Data analysis, publication development, and dissemination of findings will occur at several points, but primarily during months 53 to 60.

### Sample size

In determining sample size, we fit a linear mixed-effects model to the monthly results for assigned and available buprenorphine slots to estimate the “PRB with NIATx organizational change model” effect. The power of the study design was determined by the anticipated standardized effect size based on the effects experienced in the PRB pilot study. The PRB pilot study, which included 8 organizations, found that PRB increased physician recruitment by 43.4–100%, which can be transformed into Cohen’s *d* = .394 on average [41]. Intraclass correlation (ICC) among sites affects the power of cluster randomized trials [42]. The estimate of ICC was around 0.10. We will have recruited 35 treatment sites and 35 comparison sites. Based on our previous and current projects with similar participants, we expect about 15% attrition by the end of the data collection, so we used a more conservative 20% attrition rate for our power calculations. With 28 organizations in each condition with an average of 150 buprenorphine slots in each organization, the study will achieve a power of .93 (*d* = .30) or higher (*d* > .30) with a type I error rate of 0.05. Power calculation for the cluster RCT was performed using Optimal Design Software [43].

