### Data collection and measures

The primary outcome variables are the monthly number of (a) assigned and (b) open buprenorphine slots as well as (c) extended-release naltrexone capacity and (d) administrations over the past month. *Assigned slots* are defined as the number buprenorphine slots all prescribers affiliated with the organization have dedicated to the organization. For the buprenorphine data, on the first working Monday of the month, each organization will count the numbers of assigned and open buprenorphine slots. For extended-release naltrexone data, the number of extended-release naltrexone administrations for the previous month will be counted. These data will be collected during the 4-month planning phase, the 20-month rollout phase, and the 10-month sustainment phase, for a total of 34 months.

For the mediational analysis, at organizational baseline, mid-intervention, and the end of the intervention phases, the PRB change leader (or primary contact) will complete the organizational surveys for the PRB implementation fidelity. In addition, any physician affiliated with the organization (by employment or contract) will complete the Physician Worklife Survey [21].

The qualitative portion of the study will support the research questions by exploring facilitators and barriers to successful prescriber recruitment, as well as the process of PRB implementation within organizations and fidelity to PRB implementation sequence. Sampling for the qualitative component will promote integration of qualitative and quantitative approaches by drawing upon findings from the quantitative assessments. Semi-structured interviews will be conducted with up to 15 organizations in the intervention arm that have had success at implementing the PRB (at least 5 of the 7 practices from the PRB fidelity scale) and up to 15 organizations that have implemented fewer than 3 PRB practices at the end of the first year or mid-point of the intervention. In this longitudinal design, selected organizations will be interviewed at end of the mid-point and at the end of the intervention period to allow for more in-depth exploration of what occurred within these organizations over time.

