### Data analysis

We intend to use an optimal design in which treatment arms are allocated following a multi-site cluster randomization procedure [43]. A preliminary analysis will compare baseline characteristics between intervention and control condition sites, as well as sites enrolled in the project and eligible sites that chose to not participate. Chi-square tests and linear models will be used to formally test for statistically significant baseline differences between the arms. Descriptive statistics and plots will be used to summarize the distribution of each of the analytic variables collected at each time point for each arm. The organizational site is the unit of analysis.

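### The stated power of .93 takes the average slot count as a cluster size, so it does not apply to the organization-level analysis that is planned

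*Protocol article*

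**What the plan says.** The Sample size section assumes 35 sites per arm, reduced by 20% attrition to 28, and states "The estimate of ICC was around 0.10". It concludes: "With 28 organizations in each condition with an average of 150 buprenorphine slots in each organization, the study will achieve a power of .93". That power is attached to d = .30, "with a type I error rate of 0.05", from a cluster-trial calculation in Optimal Design. The pilot effect is given as d = .394. The same section says that a linear mixed model was fitted to monthly slot results, but gives neither a number of months nor a month-to-month correlation among the power inputs.

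Under Data collection and measures, the primary outcomes are monthly numbers per organization: "each organization will count the numbers of assigned and open buprenorphine slots" once a month, over 4 planning, 20 rollout and 10 sustainment months (34 in all). Under Data analysis, "The organizational site is the unit of analysis". The mixed models have a random effect for organization and fixed effects for arm and time. The plan names both cross-sectional models at each time point and growth models with an arm-by-time term, and it prefers autoregressive or Toeplitz errors to compound symmetry.

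**The concern.** A two-level cluster calculation needs an outcome observed on each of n members of a cluster, and an ICC describing how alike those members are. Slots are not members in that sense. A slot has no outcome of its own; it is one unit of the count that the organization reports. An ICC of slots within organizations is therefore not defined for this outcome, and a larger slot count adds no observations.

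The .93 is the only power figure given for a trial of 70 organizations. If it is taken at face value, a null result will be read as well-powered evidence of no effect, when the document does not establish what power the planned analysis has.

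**Working it through.** **Inputs from the protocol article.** 28 organizations per arm (J = 56), 150 slots per organization, ICC 0.10, d = .30 (pilot .394), alpha 0.05 (Sample size); one count per organization per month and 20 rollout months (Data collection and measures). **Assumed:** two-sided test, equal arms and, from step 3 on, d in SDs of the organization's count. The protocol does not say which SD scales d. Power is from the noncentral t with 54 df unless marked otherwise.

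**1. Reproduce the stated figure.** Noncentrality = sqrt( J × d² / {4 × [ICC + (1 − ICC)/n]} ). With n = 150 the bracket is 0.10 + 0.90/150 = 0.106, so noncentrality = sqrt(56 × 0.09 / 0.424) = sqrt(11.89) = 3.448. Power is 0.923, or 0.932 by the normal approximation. This matches .93. The alternatives miss: 34 monthly counts as cluster size at ICC 0.10 give 0.87 to 0.88, 24 months give 0.84 to 0.86, a one-sided test gives 0.96, and 35 sites per arm with n = 150 give 0.97. So 150 slots were entered as the within-cluster sample size.

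**2. What that implies.** The formula scales the variance of an organization's result to 0.106. In SDs of the organization-level result, d = .30 becomes 0.30/sqrt(0.106) = 0.92.

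**3. One count per organization, one month, unadjusted** (as in a cross-sectional model without covariates). Noncentrality = sqrt(56 × d²/4).
- d = .30: 1.122, power 0.20.
- d = .394: 1.474, power 0.31 (0.305 by t, 0.314 by normal approximation).
- The effect detectable with 80% power is 0.76 SD.

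**4. Mean of the 20 rollout months, d = .30.** Noncentrality = 1.122/sqrt(V), where V is the variance of the (adjusted) mean relative to that of a single count. With constant month-to-month correlation r:
- unadjusted: V = r + (1 − r)/20;
- adjusted for the mean of b earlier counts: V = r + (1 − r)/20 − r²/[r + (1 − r)/b].

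For AR(1) errors the same variances and covariances are computed with correlation r^|lag|. The values of r are assumed, because the protocol gives none.

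| Analysis of the 20-month mean | V at r = .5 | Power | V at r = .9 | Power |
|---|---|---|---|---|
| Unadjusted, constant correlation | 0.525 | 0.33 | 0.905 | 0.21 |
| Adjusted for one baseline count, constant correlation | 0.275 | 0.56 | 0.095 | 0.95 |
| Adjusted for mean of 4 planning months, constant correlation | 0.125 | 0.88 | 0.029 | >0.99 |
| Adjusted for mean of 4 planning months, AR(1) | 0.139 | 0.84 | 0.424 | 0.40 |

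A higher correlation raises power in the two adjusted rows with constant correlation and lowers it in the other two. The answer therefore depends on the covariance structure and the baseline adjustment as much as on the size of the correlation.

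**The case against.** The strongest reply is that the trial may well have adequate power by another route. It collects 34 monthly counts per site, and the growth models test an arm-by-time term, which removes stable differences between sites. Under constant correlation, adjusting the rollout mean for the 4 planning months gives 0.88 at r = .5, 0.97 at r = .7 and above 0.99 from r = .8. The value .30 is also already below the pilot's .394. All of this stands.

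It limits three stronger readings that a reader might infer.
- *That the true power is 0.20 and the trial is underpowered.* The documents do not support this. The 0.20 belongs to a single unadjusted month and to one reading of d; growth models are planned as well.
- *That .93 is reached only under the most favourable assumption.* The planning-month results above contradict it.
- *That slots were treated as independent.* They were correlated at 0.10, a design effect of 1 + 149 × 0.10 = 15.9; full independence would give power of about 1.00.

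The reply does not rescue the stated derivation. None of these routes uses 150 slots or a slot-level ICC, so any agreement with .93 would be coincidence. The favourable results also lean on constant correlation, which the Data analysis section sets aside in favour of autoregressive or Toeplitz errors.

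It can also be said that 70 sites have already agreed to take part and that the effect estimate and its confidence interval do not depend on this paragraph. That is true; the harm lies in how a null result would be interpreted.

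**Conclusion.** The concern holds as a mismatch between the power calculation and the planned analysis. The .93 rests on a slot-level sample size that the outcome, the unit of analysis and the model do not have, and the stated inputs do not support it. For the planned single-month comparisons, power without adjustment is 0.20 at d = .30 and 0.31 at d = .394. For the repeated-measures analyses power is unknown: in the scenarios examined it runs from 0.21 to above 0.99. These figures assume 28 sites per arm, a two-sided 0.05 test, d in organization-level SDs and month-to-month correlations of .5 to .9. The rows that use the planning months also assume that those counts are not yet affected by the intervention.

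**What to change.** Replace the slot-level calculation with an organization-level repeated-measures one. It should state:
- 28 sites per arm and one count per site per month, with the months that enter the comparison;
- the between-site SD of the count, and which SD scales d;
- the month-to-month correlation and covariance structure, consistent with the Data analysis section;
- the baseline adjustment that will be used.

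The monthly slot data that the Sample size section says were already modelled should supply these variance components. The within-site parameters take the place of the cluster size of 150 and the slot-level ICC; a within-site correlation is still needed, but of monthly counts. Report power, or the detectable difference in slots, over a stated range of correlations.

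The cost is one rewritten paragraph and one calculation. The correction does not itself require a change in the number of sites, though whether 70 is adequate can be judged only once these inputs are stated. The stated figure may become less favourable.

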### Data collection and measures

The primary outcome variables are the monthly number of (a) assigned and (b) open buprenorphine slots as well as (c) extended-release naltrexone capacity and (d) administrations over the past month. *Assigned slots* are defined as the number buprenorphine slots all prescribers affiliated with the organization have dedicated to the organization. For the buprenorphine data, on the first working Monday of the month, each organization will count the numbers of assigned and open buprenorphine slots. For extended-release naltrexone data, the number of extended-release naltrexone administrations for the previous month will be counted. These data will be collected during the 4-month planning phase, the 20-month rollout phase, and the 10-month sustainment phase, for a total of 34 months.

For the mediational analysis, at organizational baseline, mid-intervention, and the end of the intervention phases, the PRB change leader (or primary contact) will complete the organizational surveys for the PRB implementation fidelity. In addition, any physician affiliated with the organization (by employment or contract) will complete the Physician Worklife Survey [21].

The qualitative portion of the study will support the research questions by exploring facilitators and barriers to successful prescriber recruitment, as well as the process of PRB implementation within organizations and fidelity to PRB implementation sequence. Sampling for the qualitative component will promote integration of qualitative and quantitative approaches by drawing upon findings from the quantitative assessments. Semi-structured interviews will be conducted with up to 15 organizations in the intervention arm that have had success at implementing the PRB (at least 5 of the 7 practices from the PRB fidelity scale) and up to 15 organizations that have implemented fewer than 3 PRB practices at the end of the first year or mid-point of the intervention. In this longitudinal design, selected organizations will be interviewed at end of the mid-point and at the end of the intervention period to allow for more in-depth exploration of what occurred within these organizations over time.

In the interviews, the closed-ended questions will be based on domains of the Burke-Litwin Model of Organizational Change: (1) leadership, (2) recruiting practices, (3) work-unit change, and (4) organizational motivational for recruitment [44]. The open-ended questions will allow for discovery of other factors affecting PRB implementation and prescriber recruitment.

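### Naltrexone administrations are a primary outcome, but the stated baseline data leave them out and the planned models adjust for no pre-start value

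*Protocol article*

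**What the plan says.** In the protocol article, Data collection and measures lists the primary outcomes as assigned and open buprenorphine slots together with "c) extended-release naltrexone capacity and (d) administrations over the past month". The two kinds of data are counted differently. For buprenorphine it is a count on a given day: "on the first working Monday of the month, each organization will count the numbers of assigned and open buprenorphine slots". For naltrexone it looks back over a period: "For extended-release naltrexone data, the number of extended-release naltrexone administrations for the previous month will be counted". Collection runs through "the 4-month planning phase, the 20-month rollout phase, and the 10-month sustainment phase, for a total of 34 months".

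The Timeline states the pre-start data: "In months 14 to 18, the study team will collect baseline data on number of assigned and open buprenorphine slots and extended-release naltrexone capacity". Three of the four outcomes are in that sentence; administrations are not.

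Data analysis plans mixed-effects models with a random effect for organization, cross-sectional multilevel models of the arm effect at each time point, and growth curves with arm, time and their interaction. The named covariates are facility type, services offered and organizational size, plus unspecified time-varying covariates and organizational characteristics. No pre-start outcome value is among them.

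Randomization matches sites within state on the number of bundle practices in use and on whether buprenorphine is currently prescribed.

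**The concern.** For three of the four outcomes, the Timeline secures a value from before the intervention, and an analysis plan written later could adjust for it. Buprenorphine use can also be derived at baseline, as assigned minus open slots. Naltrexone use cannot be derived from anything the Timeline lists. A value that was never collected or designated is harder to add later than a model term.

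The look-back wording adds a second difficulty. A count collected early in the first study month would describe the month before the site started. It is the natural baseline, yet the article places it among the 34 months of outcome collection.

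Two things are at stake. One is precision: monthly counts from the same site are likely to be strongly related over time, and the article itself expects correlation. The other is protection against chance imbalance, since neither matching factor measures naltrexone use and the number of sites is modest.

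**Working it through.** **Inputs.** Phases of 4, 20 and 10 months, and the look-back rule (Data collection and measures). Baseline in project months 14 to 18, and a 24-month staggered-start intervention within project months 15 to 42 (Timeline). 35 sites per arm and a 20% attrition allowance (Sample size). Assumed, because the article does not give them: the month to which a count is assigned, and the correlation r between a pre-start count and a later count.

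**1. The plan's own total.** 4 + 20 + 10 = 34 months. It reproduces.

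**2. Months covered by the look-back counts.** A count collected in study month m covers month m − 1.

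| Reading | Months covered | Pre-start counts |
|---|---|---|
| Collected in months 1–34 | 0–33 | 1 of 34 (2.9%) |
| Collected in months 2–35, or at the end of each month 1–34 | 1–34 | 0 |

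Under the first reading, if counts were also kept under the month of collection, the phases would hold months 0–3 (planning), 4–23 (rollout) and 24–33 (sustainment). That puts 1 of 4 planning values before the start and makes 1 of 10 sustainment values the last intervention month. If counts are indexed to the month of injection, neither mislabelling occurs.

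**3. Where month 0 falls.** A 24-month intervention that ends by project month 42 starts no later than 42 − 24 + 1 = 19, so starts lie in months 15 to 19. Month 0 is then project month 14 to 18, which is the Timeline's baseline window. Under the first reading, the first look-back count is a usable baseline that is not called one. Under the second, the listed data contain no pre-start value of naltrexone use. Either way, none is declared.

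**4. Precision.** In a cross-sectional comparison, adjusting for a pre-start count with correlation r leaves a fraction 1 − r² of the between-site variance. The standard error is multiplied by √(1 − r²).

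| Assumed r | Variance left | Standard error factor |
|---|---|---|
| 0.5 | 1 − 0.25 = 75% | 0.87 |
| 0.7 | 1 − 0.49 = 51% | 0.71 |
| 0.9 | 1 − 0.81 = 19% | 0.44 |

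**5. Chance imbalance.** Ignoring matching, the standard error of the arm difference in a baseline measure, in between-site standard deviations, is √(2/n). For n = 35 it is √(2/35) = 0.24. For n = 35 × 0.80 = 28 it is √(2/28) = 0.27. Matching reduces this only so far as the matching factors predict naltrexone use, which the article does not report.

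**The case against.** The strongest objection is that this is a small omission in a condensed article. The full protocol may collect the value, month indexing is the sort of detail left to it, and Data analysis promises a comparison of baseline characteristics without listing them. That disposes of any complaint about indexing as such. It does not remove the gap in the Timeline, which gives an explicit list that omits one primary outcome.

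A second objection is that Data analysis states no baseline-outcome adjustment for any outcome, so naltrexone is not treated worse in the models. In the growth curves, moreover, stable site differences are taken up by the random effect, and the arm-by-time term is largely protected from a difference in level. This stands for the growth curves. It does not cover the cross-sectional contrasts, and only for naltrexone use is the baseline value itself missing from the stated data.

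Several stronger inferences are tempting but not supported:

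- **That counts are filed under the wrong month, so the series covers months 0–33 and month 34 is lost.** No section states the month assignment, and the first-Monday rule is given for buprenorphine only. These statements are conditional.
- **That no baseline exists.** If the first count is from month 0, it supplies one; it is only undesignated.
- **That the lag biases the arm comparison.** It is one month and the same in both arms. A slot count on the first Monday of month 1 is also nearly pre-intervention, so an early first record is not peculiar to naltrexone.
- **That a second baseline list repeats the omission.** The planning-phase step to "document the existing buprenorphine slots availability and extended-release naltrexone capacity" belongs to the coached process described for the intervention arm. It is not a data list for both arms.
- **That matching rests on buprenorphine alone.** It also uses the number of bundle practices in use.

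**Conclusion.** The point holds in a limited form. Naltrexone administrations are a primary outcome without a declared pre-start value, and the stated covariates would not adjust for one. The consequence is forgone precision and weaker protection against chance imbalance with 28 to 35 sites per arm; no bias or inflated type I error is shown. The size of the gain depends on an unknown correlation: over the assumed range of 0.5 to 0.9, between 75% and 19% of the between-site variance would remain in a cross-sectional contrast.

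The month question is secondary. If collection runs in study months 1 to 34, one of 34 outcome counts precedes the start; under the other readings none does. The conclusion about the missing declared baseline is the same under every reading. It assumes that the full protocol, which is not shown, does not already record the value.

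**What to change.** - Add naltrexone administrations in the month before start to the baseline data in the Timeline, in both arms and by the same rule for each. Alternatively, designate the first look-back count as that baseline and remove it from the outcome series, leaving 33 outcome counts. This alternative works only if collection begins in study month 1.
- Include that value as a covariate in the naltrexone-use models, above all in the cross-sectional ones.
- State that each count is indexed to the month in which the injections were given.

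The cost is one baseline field, one covariate and one sentence on indexing. Trial status says that baseline collection has only begun, so the field can probably be completed from site records; that is an assumption. No additional report after month 34 is needed.
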